# Liraglutide efficacy and action in non-alcoholic steatohepatitis (LEAN): study protocol for a phase II multicentre, double-blinded, randomised, controlled trial

**DOI:** 10.1136/bmjopen-2013-003995

**Published:** 2013-11-04

**Keywords:** Clinical Pharmacology, Histopathology

## Abstract

**Introduction:**

Non-alcoholic steatohepatitis (NASH) is now the commonest cause of chronic liver disease. Despite this, there are no universally accepted pharmacological therapies for NASH. Liraglutide (Victoza), a human glucagon-like peptide-1 (GLP-1) analogue, has been shown to improve weight loss, glycaemic control and liver enzymes in type 2 diabetes. There is currently a lack of prospective-controlled studies investigating the efficacy of GLP-1 analogues in patients with NASH.

**Methods and analysis:**

Liraglutide efficacy and action in NASH (LEAN) is a phase II, multicentre, double-blinded, placebo-controlled, randomised clinical trial designed to investigate whether a 48-week treatment with 1.8 mg liraglutide will result in improvements in liver histology in patients with NASH. Adult, overweight (body mass index ≥25 kg/m^2^) patients with biopsy-confirmed NASH were assessed for eligibility at five recruitment centres in the UK. Patients who satisfied the eligibility criteria were randomly assigned (1:1) to receive once-daily subcutaneous injections of either 1.8 mg liraglutide or liraglutide-placebo (control). Using A'Hern's single stage phase II methodology (significance level 0.05; power 0.90) and accounting for an estimated 20% withdrawal rate, a minimum of 25 patients were randomised to each treatment group. The primary outcome measure will be centrally assessed using an intention-to-treat analysis of the proportion of evaluable patients achieving an improvement in liver histology between liver biopsies at baseline and after 48 weeks of treatment. Histological improvement will be defined as a combination of the disappearance of active NASH and no worsening in fibrosis.

**Ethics and dissemination:**

The protocol was approved by the National Research Ethics Service (East Midlands—Northampton committee; 10/H0402/32) and the Medicines and Healthcare products Regulatory Agency. Recruitment into the LEAN started in August 2010 and ended in May 2013, with 52 patients randomised. The treatment follow-up of LEAN participants is currently ongoing and is due to finish in July 2014. The findings of this trial will be disseminated through peer-reviewed publications and international presentations.

**Trial registration:**

clinicaltrials.gov NCT01237119.

## Introduction

Non-alcoholic fatty liver disease (NAFLD) is now the commonest cause of chronic liver disease, affecting up to 30% of the general population^1–3^ and 70–90% of high-risk individuals.^3^
^4^ This prevalence relates to the dramatic rise in recent years of morbid obesity and type 2 diabetes (T2D). Even though simple hepatic steatosis (without fibrosis) is arguably a benign condition, up to a quarter of patients with NAFLD have the more severe, inflammatory condition known as non-alcoholic steatohepatitis (NASH).^5^ Patients with NASH have an increased risk of progression to cirrhosis, liver failure and hepatocellular carcinoma,^6^ and are expected to become the commonest indication for liver transplantation in forthcoming years.^7^ Despite this, there are no universally accepted pharmacological therapies for NASH. Therefore the need for novel, safe agents in NASH is of paramount importance to prevent disease progression and the accompanying clinical burden.

The strong association of NASH with metabolic syndromes, in particular central adiposity and insulin resistance, provides a strong rationale for investigating therapies that induce weight loss and insulin sensitivity. The gut-derived incretin hormone, glucagon-like peptide-1 (GLP-1), is therefore an attractive target option in NASH. Native GLP-1 has a potent blood glucose-lowering action mediated through its ability to induce insulin secretion and reduce glucagon secretion in a glucose-dependent manner, as well as suppressing appetite and slowing gastric emptying.^8^ Human GLP-1, however, only has a short half-life (1.5–2 min) as it is rapidly degraded by the enzyme dipeptidyl peptidase-4 (DPP-4).^9^ Liraglutide (Victoza) is a long-acting (half-life 13 h) GLP-1 analogue with 97% structural homology to the native hormone and is administered once daily by subcutaneous injection.^10^ Liraglutide has been shown to cause dose-dependent weight loss,^11^
^12^ decrease glycosylated haemoglobin (HbA1c), systolic blood pressure and improve β-cell function.^13–18^ Subsequently, it has been licensed for glycaemic control in overweight patients with type 2 diabetes (T2D).^19^ There is, however, a paucity of data in patients with liver disease, and in particular histologically defined NASH.

GLP-1 analogues, including liraglutide, have been shown to improve liver enzymes, oxidative stress and hepatic steatosis in murine models in vivo and in isolated in vitro murine and human hepatocyte studies.^20–25^ To date, human studies investigating the effect on liver injury have been limited to case reports,^26^
^27^ solitary case series (n=8)^28^ and retrospective (*liver enzyme*) studies in patients with T2D.^29^ A large meta-analysis of six phase III randomised controlled trials (RCT), that comprised the Liraglutide Effect and Action in Diabetes (LEAD) programme (>4000 patients), highlighted that the 26-week treatment with 1.8 mg once daily liraglutide was well-tolerated and resulted in significant improvements in liver enzymes compared to placebo control in overweight patients with T2D.^30^ However, limitations of this study were the retrospective nature of its analysis and the lack of any liver biopsy data.

On this basis, we hypothesised that the 48-week treatment with liraglutide would result in significant improvements in liver histology in overweight patients with NASH. To test this hypothesis, we designed a phase II, multicentre, double-blinded, placebo-controlled RCT, entitled ‘Liraglutide Efficacy and Action in NASH (LEAN).’

## Methods

### Study design overview

LEAN is a 48-week multicentre, double-blinded, placebo-controlled randomised clinical trial of treatment with the once daily human GLP-1 analogue, liraglutide (Victoza), for adults with biopsy-proven NASH. Screening was undertaken within 14 days of randomisation to assess eligibility and collect baseline data. Patients who satisfied the eligibility criteria were randomly assigned (1:1) to receive subcutaneous injections once daily of either 1.8 mg liraglutide (experimental) or liraglutide-placebo (control). After which, a 12-week washout period is scheduled.

The primary outcome measure will be assessed using an intention-to-treat analysis of the proportion of evaluable patients achieving an improvement in liver histology between liver biopsies at baseline (within 6 months of screening) and after 48 weeks of treatment. Histological improvement will be defined as a combination of the disappearance of active steatohepatitis (ie, disappearance of hepatocyte ballooning) and no worsening in fibrosis (Kleiner Fibrosis score^31^). A schematic of the trial design is summarised in figure 1.

**Figure 1 BMJOPEN2013003995F1:**
[figure not shown]
Schematic of liraglutide efficacy and action in non-alcoholic steatohepatitis trial design. Eligible participants are randomly assigned to a 48-week treatment of once daily subcutaneous injections of either 1.8 mg liraglutide or placebo control. Both the trial investigators and the participants are blinded to drug allocation.

### Ethical and regulatory approval

The National Research Ethics Service (NRES) East Midlands—Northampton committee (previously known as Leicestershire, Northamptonshire and Rutland Research Ethics Committee, UK) and the Medicines and Healthcare products Regulatory Agency (MHRA) approved all versions (including current V.7.0) of the study protocol. In addition, all five recruitment sites obtained approval from their respective hospital Research and Development (R&D) departments prior to the start of screening.

### Treatment groups

Patients who satisfied the eligibility criteria were randomly assigned on a 1:1 basis to a 48-week treatment of either liraglutide (Victoza; 1.8 mg once daily) or liraglutide-placebo control (1.8 mg once daily).

#### Liraglutide (active experimental group)

Liraglutide (Victoza, Novo Nordisk A/S, Bagsvaerd, Denmark) was supplied in a cartridge contained in a prefilled multidose disposable pen. Each prefilled pen contained 18 mg liraglutide in 3 mL of clear, colourless, isotonic solution (including water for injections, disodium phosphate dehydrate, propylene glycol and phenol). Liraglutide was administered once daily, at any time of the day, as a single subcutaneous injection into the abdomen, thigh or upper arm using the prefilled pen (30 or 31 gauge needles). Participants were encouraged to inject liraglutide at the same time each day, according to the most convenient time for them. Participants were instructed to perform an air shot of 0.2 µL before the first use of each new prefilled pen to ensure that it functioned correctly.

To improve gastrointestinal tolerability participants underwent a 14-day dose-titration period in keeping with previous reports.^13–18^ The dose was titrated by 0.6 mg every 7 days from a starting dose of 0.6 mg once daily until the maximum dose of 1.8 mg once daily was achieved. Prior to the current trial design, no study had investigated any form of GLP-1-based therapy in patients with biopsy-confirmed NASH or any other form of liver disease. Therefore, the rationale for using a dose of 1.8 mg once daily was based on previous reports in overweight patients with or without T2D.^13–18^ Furthermore, a large meta-analysis of six phase III clinical trials (LEAD programme) of liraglutide therapy for poorly controlled T2D found that patients with abnormal liver transaminases had a similar drug safety profile to those with normal liver transaminases. In addition, greater improvements in liver transaminases and CT-measured hepatic steatosis were seen with 1.8 mg liraglutide than 1.2 and 0.6 mg doses.^30^

#### Liraglutide-placebo (inactive, placebo-control group)

Liraglutide-placebo (Victoza, Novo Nordisk A/S, Bagsvaerd, Denmark) was packaged, administered and dose-titrated in an identical manner to the liraglutide comparator, described above. The composition of the placebo solution for injection was identical to its comparator, with the exclusion of the active liraglutide substance. A placebo was used to provide an assessment of the level of response with an injectable placebo, which could potentially be higher than that seen with oral placebo agents.

#### Concomitant therapy

No dose reductions of liraglutide or placebo were allowed throughout the 48-week treatment period. Previous treatment with oral antidiabetic drugs (metformin and/or sulfonylurea) was continued at the same dose in participants with T2D at randomisation. In the event of recurrent major hypoglycaemic episodes (requiring medical or hospital intervention), the dose of the sulfonylurea was reduced by 50% at the discretion of the investigators. The reported rate of hypoglycaemia in literature, with liraglutide monotherapy or in combination with metformin, is very low.^13–18^ However in the event of recurrent major hypoglycaemic episodes in which no dose reduction could be undertaken (ie, not on a sulfonylurea) the participant was withdrawn from treatment at the discretion of the chief investigator.

Glycaemic control was assessed at each 12-weekly trial visit with self-measured plasma glucose readings and HbA1c. In the event that glycaemic control deteriorated, defined as HbA1c >9% (75 mmol/mol), the participant was informed and counselled with regard to starting open-labelled long-acting insulin detemir once daily (Levemir). However, the patient's participation in the trial was not jeopardised if they did not wish to start insulin detemir. The insulin detemir dose was titrated by trial investigators in accordance with European guidelines (http://www.ema.europa.eu) to ensure that the participant's standard of diabetes care was not significantly compromised as a result of participating in the clinical trial. The HbA1c cut-off >9% was based on the opinions of the TMG ([name] and [name]), consisting of expert endocrinologists ([name] and [name]), and in accordance with previous clinical trial guidance.^32^

In addition to study medications, participants continued to receive standard National Health Services (NHS) care recommendations concerning life-style modifications (ie, exercise, weight loss and dietary modification) and management of various coexisting illnesses throughout the trial. Patients were asked to limit alcohol consumption to less than 20 mg/day for women (ie, 14 units/week) and 30 mg/day for men (ie, 21 units/week). These levels were consistent with the UK Department of Health recommended daily alcohol allowance (British Medical Association 1995). Participants were not allowed any new prescription or over-the-counter therapies (ie, herbal remedies, milk thistle) that may improve or worsen NASH throughout the duration of the trial. Potential NASH therapies that were not allowed during the trial duration included thiazolidinediones (TZDs), DPP-4 inhibitors, other GLP-1 receptor agonists (eg, exenatide), vitamin E and orlistat. Steroids (oral or intravenous), methotrexate and/or amiodarone were also not permitted based on their ability to promote hepatic steatosis.

### Outcome measures

#### Primary outcome measure

The primary outcome measure is the proportion of participants with a significant improvement in liver histology between liver biopsies at baseline (ie, within 6 months of screening) and at the end of a 48-week treatment. The definition of a significant histological improvement requires both the disappearance of steatohepatitis (defined as a disappearance of hepatocyte ballooning) and no worsening of fibrosis, as assessed by the Kleiner scoring system.^31^ Hepatocyte ballooning is now widely recognised as the key lesion for distinguishing NASH from simple steatosis.

#### Secondary outcome measures

Secondary outcome measures include changes in; (1) overall NAFLD Activity Score (NAS)^31^; (2) individual histological components of NAS, including lobular inflammation, steatosis, hepatocyte ballooning and fibrosis; (3) serum markers of steatosis (SteatoTest), NASH (NashTest, caspase-cleaved cytokeratin-18 (CK-18 M30)) and fibrosis (Enhanced Liver Fibrosis (ELF; iQUR Ltd), FibroTest); (4) liver stiffness evaluation (LSE) with Transient Elastography (Fibroscan, Echosens, Paris, France); (5) insulin resistance (HOMA-IR); (6) anthropometric measures including body weight, body mass index (BMI) and waist circumference; (7) lipid profile and glycaemic control (HbA1c, fasting plasma glucose); (8) serum alanine aminotransferase levels and (9) health-related quality of life (QOL; SF-26 V.2.0) and nutrition (Block Brief 2000 Food Frequency Questionnaire (FFQ) questionnaires).

### Analytical methods

#### Liver histopathology

Two independent liver histopathologists ([name] and [name]) at the central trial site (Birmingham, UK) will perform all the histopathological assessments using an in-house designed proforma (see online supplementary table S1). Both histopathologists will be blinded to the clinical, laboratory and study treatment allocation. The histological diagnosis of NASH will be established using H&E staining and haematoxylin van Gieson stains of formalin-fixed paraffin-embedded liver tissue. Both the baseline and end-of-treatment (48 weeks) biopsies will be reported as either ‘definite NASH,’ ‘uncertain NASH’ or ‘not NASH.’ The histological diagnosis of ‘definite NASH’ is defined as a combination of >5% macrovesicular steatosis, hepatocyte ballooning (± Mallory's Hyaline) and lobular inflammation (mixed infiltrate, related to foci of ballooning).^33^ The assessment of ballooning is subjective, and thus for ‘uncertain’ hepatocyte ballooning, a key component of the diagnosis of NASH, ubiquitin immunohistochemistry will be used to identify material compatible with Mallory's hyaline (figure 2). To validate the quality of the biopsy specimen, the core specimen length will be measured and the number of portal tracts will be recorded.

**Figure 2 BMJOPEN2013003995F2:**
[figure not shown]
Histological inclusion criteria for liraglutide efficacy and action in non-alcoholic steatohepatitis (LEAN) trial. Liver biopsy sections (actual magnification ×400). (A and B) ‘Uncertain’ non-alcoholic steatohepatitis (NASH)—not eligible for LEAN: (A) H&E stain highlights fat, inflammation and some pale cells, however (B) ubiquitin immunohistochemistry does not identify any Mallory Denk bodies (no confirmed ballooning). (C and D) ‘Uncertain’ NASH—eligible for LEAN: (C) H&E stain highlights fat, inflammation and pale cells, but with no obvious Mallory Denk bodies. However, ubiquitin staining (D) is positive (confirming ballooned hepatocytes). (E,F) ‘Definite’ NASH—eligible for LEAN: both H&E and ubiquitin staining highlight fat, lobular inflammation and widespread ballooned hepatocytes. Black arrows highlight Mallory Denk bodies.

The NAS will be calculated based on the Kleiner classification.^31^ The NAS is scored of 8, with 8 representing the highest activity. The NAS is the sum of scores of the 3 components of the histological scoring system, namely steatosis (0=<5%, 1=5–33%, 2=>33–66%, 3=>66%), lobular inflammation (0=no foci, 1=<2 foci/×200, 2=2–4 foci/×200, 3=>4 foci) and hepatocyte ballooning (0=none, 1=few ballooned cells, 2=many cells/prominent ballooning). The Kleiner scoring system for NAFLD fibrosis (F0-F4)^31^ and a modified version of the Ishak score^34^ (F0-F6; see online supplementary table S1) will be used to evaluate the stage of fibrosis in each biopsy specimen. The Ishak score was modified from the original scoring system, reported in 1995,^34^ in order to include the zone 3 peri-cellular/peri-sinusoidal fibrosis, which is characteristically seen in NASH. Portal tract changes (inflammation, interface hepatitis, ductular reaction), an intrinsic feature of NASH, will also be recorded.^35^

The pathologists will assess the biopsies independently and fill in separate forms. Cases where there is disagreement on the classification, as ‘NASH’ or ‘not NASH,’ will be reviewed and a consensus opinion given. Also discrepancies of more than 1 point on any of the scoring scales (NAS, Kleiner fibrosis scoring system and modified Ishak score) will be reviewed and an amended consensus view offered. Discrepancies of only 1 point will not be altered.

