### Analysis of outcome measures

All evaluable patients will be analysed on the intention-to-treat principle. Evaluable patients are defined as those who have had an end-of-treatment biopsy (visit 7), irrespective of the amount of treatment they have received. Patients will be categorised as either achieving the primary histological endpoint (ie, disappearance in NASH) or not. The proportion of patients with a reported improvement in liver histology will be presented and compared across treatments descriptively with 95% CIs. The proposed A'Hern's design stipulates that 8 or more evaluable patients of 21 in the experimental treatment group (liraglutide) need to achieve the defined improvement in liver histology for treatment with liraglutide to be deemed worthy of further investigation with a phase III trial. Analyses will be presented for the subgroups of patients with and without T2D. Patients who have not had an end-of-treatment biopsy will be classed as non-evaluable and will not be included in the primary analysis.

Secondary analysis of the primary outcome measure will report (1) the number and proportion of patients that did not have an end-of-treatment biopsy and the reasons for this (these will be classified as ‘no histological improvement’) and (2) the number and proportion of patients that were considered to have had sufficient treatment and an end-of-treatment biopsy. In addition, an analysis that directly compares the two proportions for the separate treatment arms will be performed using the χ^2^ test.

Secondary measures collected as continuous and categorical variables will be presented with 95% CIs descriptively across treatments using medians and proportions, respectively. Secondary measures collected as longitudinal data (including QOL data, scored as per the questionnaire-specific scoring manuals) will be presented descriptively across treatment groups as changes over time. A summary of all adverse events (AEs) experienced by patients in both arms will be reported.

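### One-stage Kleiner fibrosis disagreements between the two readers are left standing although one stage decides primary response, and the article gives no rule for turning two readings into one status

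*Protocol article*

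**What the plan says.** All references are to the protocol article.

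- **Endpoint** (Primary outcome measure). Response "requires both the disappearance of steatohepatitis (defined as a disappearance of hepatocyte ballooning) and no worsening of fibrosis", with fibrosis judged on the Kleiner scale.
- **Scales** (Liver histopathology, text after Figure 2). Ballooning has three levels: "hepatocyte ballooning (0=none, 1=few ballooned cells, 2=many cells/prominent ballooning". Fibrosis is staged as follows: "The Kleiner scoring system for NAFLD fibrosis (F0-F4".
- **Reading** (same place). "The pathologists will assess the biopsies independently and fill in separate forms".
- **First consensus trigger** (same place). "Cases where there is disagreement on the classification, as ‘NASH’ or ‘not NASH,’ will be reviewed and a consensus opinion given".
- **Second consensus trigger** (same place). Differences of more than one point on the NAS, the Kleiner stage or the modified Ishak score are reviewed. The paragraph then ends: "Discrepancies of only 1 point will not be altered".
- **Patient-level call** (Analysis of outcome measures). "Patients will be categorised as either achieving the primary histological endpoint (ie, disappearance in NASH) or not". The go rule in the same section is at least 8 responders among 21 evaluable liraglutide patients.

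**The concern.** The threshold for adjudication (more than one point) is coarser than the threshold that decides the endpoint (one Kleiner stage). A one-stage disagreement is the smallest that can occur. The rule leaves exactly that disagreement in place, while the analysis needs a single yes or no for each patient. Averaging the two readers can serve a summary score such as the NAS. It does not settle a binary call: a mean change of half a stage is neither worsened nor not worsened until someone sets a cut.

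At stake is the count of responders that drives the go decision. If the handling of split patients is not fixed in advance, the count has more than one defensible value.

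**Working it through.** **1. Which splits escape review?**

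| Reader 1 | Reader 2 | NASH / not-NASH trigger | More-than-one-point trigger | Responder status |
|---|---|---|---|---|
| Ballooning cleared, F2 to F2 | Ballooning cleared, F2 to F3 | Does not fire: fibrosis is not part of the NASH definition | Does not fire: difference is 1 | Yes versus no, unresolved |
| Week-48 ballooning 0, not NASH | Week-48 ballooning 1, definite NASH | Fires | Not needed | Goes to consensus |
| Week-48 ballooning 0, not NASH | Week-48 ballooning 1, uncertain NASH | Not named in the trigger | Does not fire on this 1-point split | Open |
| Week-48 ballooning 0, not NASH | Week-48 ballooning 1, not NASH because another criterion is absent | Does not fire | Does not fire on this 1-point split | Open |

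The ballooning rows assume that fibrosis has not worsened and that the other scores do not themselves trigger a review. Row 2 is the usual ballooning case, because Liver histopathology makes ballooning necessary for definite NASH. One loose end remains even there: a consensus on the classification is not said to reset the ballooning score, and it is the ballooning score that defines the endpoint.

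**2. The plan's own design.** Inputs from Sample size justification and Analysis of outcome measures: null rate 0.20, target rate 0.50, significance level 0.05, power 0.90, n = 21, cut-off 8. Let X be binomial with n = 21.

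- P(X ≥ 8 | 0.20) = 0.0431, within 0.05.
- P(X ≥ 8 | 0.50) = 0.9054, above 0.90.
- A search over n gives 21 with cut-off 8 as the smallest design meeting both limits.

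The stated design reproduces.

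**3. Width of the decision boundary.** 7/21 = 33.3% is a no-go and 8/21 = 38.1% is a go. With seven agreed responders and one split patient, the handling of that patient is the decision.

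**4. How likely is at least one split patient?** No discordance rate is given, so the share d of patients with opposite responder calls is assumed. P(at least one of 21) = 1 − (1 − d)^21:

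- d = 2%: 34.6%
- d = 5%: 65.9%
- d = 10%: 89.1%

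**5. Illustrative effect on the error rates.** An open fibrosis split matters only where ballooning has cleared. Assume 25% clear ballooning under the null. If 10% of those are split on fibrosis, the responder split is 0.25 × 0.10 = 2.5 percentage points; at 20% it is 0.25 × 0.20 = 5 points. Count every split patient as a responder on top of 20% agreed responders:

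- P(X ≥ 8 | 0.225) = 0.0788
- P(X ≥ 8 | 0.25) = 0.1299

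In the other direction, start from a 50% response rate and count the same 2.5 or 5 points as failures:

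- P(X ≥ 8 | 0.475) = 0.8605
- P(X ≥ 8 | 0.45) = 0.8029

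Both directions are extremes, because every split patient is resolved the same way.

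**The case against.** **The classification trigger already covers ballooning.** Largely true. The trigger applies whatever the point difference, and uncertain ballooning is also sent to ubiquitin staining. A reader might infer that every ballooning split of 0 versus 1 is left unresolved; the text does not support that. Only the residue in the working stays open. Inclusion criteria does treat uncertain versus definite as a disagreement needing joint review, but for eligibility, not for week 48.

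**Leaving scores unaltered does not bar a later derivation rule.** This stands. A reader might infer that the article forbids reconciling the readings. It says only that the recorded scores stay as they are. The full protocol (V.7.0) or an analysis plan, neither shown, may name the value to be used, so the gap can be asserted only of this article. It is still more than omitted detail: the article spells out its adjudication rule, and the threshold stated there does not fit the endpoint.

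**Nothing suggests the choice would favour liraglutide.** This stands. A reader might infer that split patients would be classified once the readings were known. The article does not say when the call is made; both pathologists are blinded, and so is most of the trial management group.

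**Large effects on error rates are not supported.** Adding 10 points of split patients to the 20% null would give a go probability of 27.7%, and taking 10 points off 50% would give power of 65.0%. Those figures rest on an unsourced discordance rate applied to all patients, all in one direction. They should not be read as estimates.

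**The analysis section has not dropped the fibrosis criterion.** Agreed. Its parenthesis names only the disappearance of NASH, but it glosses an endpoint defined in full in the Abstract, Study design overview and Primary outcome measure. It is loose shorthand.

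**Conclusion.** The point holds for fibrosis. A one-stage Kleiner disagreement can reverse responder status in a patient whose ballooning has cleared, it triggers no consensus, and the article has no rule for turning the two readings into the single status that the analysis requires. For ballooning only a residue is open: cases involving uncertain NASH, cases where both readers say not NASH yet differ on ballooning, and the unstated link from classification consensus to the ballooning score.

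The consequence that needs no assumption about rates is that the go boundary is one patient wide, so one split patient can decide the result when the agreed count is seven. The change in the go probability from 4.3% to 7.9–13.0% is illustrative. It assumes 25% ballooning clearance under the null, 10–20% fibrosis discordance among those patients, and every split counted as a response. The documents supply none of these figures. A reader might infer that the sample size is affected; it is not, since 21 patients with a cut-off of 8 reproduces exactly.

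**What to change.** Amend the consensus rule in Liver histopathology so that any disagreement that changes primary responder status goes to the joint blinded review by the same two pathologists, and the consensus value is used for the primary endpoint. The triggering disagreements are:

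- Kleiner stage worsened versus not worsened from baseline to week 48;
- ballooning 0 versus 1 or more at week 48, including where either reader classifies the biopsy as uncertain NASH.

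Other one-point differences may stand as recorded. Put the rule in place before unblinding; Trial status reports follow-up still under way, with the last visit due in July 2014.

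As an editorial tidy-up, Analysis of outcome measures should refer to the full two-part endpoint definition in place of the short gloss.

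The cost is a wording change and a few extra joint reviews. No new readers, biopsies or patients are needed.
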